4.1.1. Blinding procedures

It is not possible to blind the patient towards type of treatment (sleep deprivation or exercise). It is, however, possible to blind a permanent rater towards the treatment the patient has received. This can be done by having a rater who interviews and rates the patient each time throughout the whole study period by means of the Hamilton scale. The patients will be informed that they are not to disclose the type of treatment they receive to this permanent rater who assesses severity of depression according to Hamilton. There is no item in the Hamilton scale to reveal the type of treatment the patient receives, not even the sleep item, as all patients record their sleep in a sleep diary. The rater who conducts the interview will not meet the patient in the ward, as the regular visits are outside (before and after) the period of hospitalisation and will not be permitted to see patient records or CRFs. This rater will only receive the Hamilton rating sheet which does not contain information as to treatment group. All other procedures of the study will be performed by unblinded evaluators.

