**4.3. Efficacy parameters**

4.3.1 The primary efficacy parameter is the number of patients in the two group that have achieved response to treatment or remission after 2, 9 or 29 weeks. Response is defined as a more than 50% reduction in HAM-D17 scores after inclusion into the study while remission is defined as a score of 7 or less on the HAM-D17.

4.3.2. Secondary effect parameter is the number of those patients in the two treatment groups who have experienced long-lasting response or remission after 9 weeks and after 29 weeks. Lasting response is defined as patients responding after 2 weeks of enrolment in the study and the response either lasting until week 9 (early lasting response) or until week 29 (episode response). Lasting remission is defined as being in remission after 2 weeks in the study and the remission either lasting until week 9 (early lasting remission) or until week 29 (episode remission). Response and remission are defined as mentioned under primary efficacy parameter. Patients who according to the protocol receive further sleep deprivations in week 4, 5, or 6 thus are cannot be defined as being in early, lasting remission. Response and emission are defined as mentioned under primary efficacy parameter. Patients who according to the protocol carry out additional sleep deprivation in weeks 4, 5 or 6 thus are defined not to be in early lasting remission.

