4.6.5. Criteria for discontinuation of study treatment (end-points)

- The wish to discontinue treatment (sufficient follow-up treatment will be secured). In case of a waiting period treatment will be provided by the Psychiatric Research Unit.
- Patients with intolerable or clinically significant side effects.
- Patients who at any time during the first 9 weeks of the study have score of 15 or more on the Mania Scale (MAS) irrespective of a mania or hypomania diagnosis.
- Patients who display a continued clinical worsening of their depression at two subsequent weekly assessments (first nine weeks of the study).
  - Patients who after the primary hospitalisation experience a worsening of their depression and have to be re-admitted (first 9 weeks).
  - Mania requiring hospitalisation (first 9 weeks).
  - Change of mood stabilizer in bipolar patients (whole study).
  - Patients who do not comply with the single elements of the study will in general be discontinued (but see also "protocol deviations")

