4.6.6. Protocol deviations

The following protocol deviations do not mean exclusion from the study:

- - Skipping maximum one of three sleep deprivations in week 2.
  - Not taking up to 15% of the study drug duloxetine (first 9 weeks).
  - Not taking up to 15 % of other prescribed medication. (whole study period).
  - Skipping maximum 2 visits during the first 9 weeks and 2 visits during the following weeks until week 29.

When a patient discontinues participation in the study, this is recorded in the CRF together with the reason for drop-out and the type of follow-up. An individual assessment will decide whether to collect raw data from the last visit (exclusion visit) or from the last previous regular visit.

Collecting last visit data requires that the medicine prescribed has been taken according to the guidelines for compliance.

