**11. STATISTICS**

To analyse the number of patients with response or remission at three defined points in time (weeks 2, 9 and 29), Chi2 distribution is used. To do this, the Last Observation Carried Forward (LOCF) is employed. The assessment of the longitudinal courses of response and remission (and sustained response and remission) uses survival analysis (Kaplan-Meier survival-analysis) including log-rank test to calculate p values (Stassen et al 1993). Furthermore, the Mixed Model Repeated Measures (MMRM) (Brown et al. 1999) will analyse readily available depression scores to determine the difference between the two groups. Thus, MMRM does not use LOCF. The association between cortisol and depression scores and the association between urine and saliva cortisol has been calculated by means of the Spearman correlation coefficient *rho*. The same statistical method will be used to test the association between the various degrees of depression and the effect of sleep deprivation. The idiographic method will be analysed by means of MMRM. Exercise will be analysed as the percentage of compliance to the predefined goal (30 minutes exercise daily). Moreover, the achieved amount of exercise (combined score of the Borg scale and the amount of performed exercise) will be graded into light/moderate/intensive in follow-up phase I. It will be compared with the degree of response and remission in week 29 and analysed by Chi2 distribution. The number of study subjects has been calculated on the basis of an expected depression score of 24 on the 17-item Hamilton Depression Scale at inclusion into the study for both groups. After 9 weeks of treatment a decrease to 10 in group A and to 13 in group B is expected. The expected standard deviation is 4. With a type-I error of 0.05 and 0.90 power, 39 patients are required for each group.

No interim analyses have been planned.

GCP guidelines permit that patients may be excluded from the data analysis after the end of the study, if eligibility violations have taken place and if this was not known during the project. This may refer patients who have fulfilled the inclusion criteria, but have not taken any of the study medication, or have taken other prescriptions without telling the investigator, and where these violations were not known until the end of the study. All other patients assessed at the time of inclusion in the study are included in the statistical analyses according to the intention-to-treat method.

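### Section 4.6.6 lets a case-by-case assessment, plus a medication-compliance condition, decide which visit supplies a discontinued patient's data, and LOCF can carry that value into the primary responder tests.

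*Protocol*

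**What the plan says.** All references are to the protocol.

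- Section 4.3 defines the primary outcome as counts: "The primary efficacy parameter is the number of patients in the two group that have achieved response to treatment or remission", assessed at weeks 2, 9 and 29. Response is a fall of more than 50% in HAM-D17; remission is a score of 7 or less.
- Section 11 tests these counts by chi-square and says of missing values: "To do this, the Last Observation Carried Forward (LOCF) is employed".
- Section 4.6.6 says where a discontinued patient's data come from: "An individual assessment will decide whether to collect raw data from the last visit (exclusion visit) or from the last previous regular visit". It adds one condition: "Collecting last visit data requires that the medicine prescribed has been taken according to the guidelines for compliance".
- Section 11 sets the analysis population. It first allows removal of patients for certain violations that come to light only once the trial is over, and then states: "All other patients assessed at the time of inclusion in the study are included in the statistical analyses according to the intention-to-treat method".
- Section 4.1.1 blinds the permanent Hamilton rater, who may not see patient records or CRFs. Of everything else it says: "All other procedures of the study will be performed by unblinded evaluators".
- Section 4.6.5 lists reasons for discontinuation. They include, in the first nine weeks, "Patients who display a continued clinical worsening of their depression at two subsequent weekly assessments", worsening that needs readmission, and a Mania Scale (MAS) score of 15 or more. They also include non-compliance: "Patients who do not comply with the single elements of the study will in general be discontinued".

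**The concern.** LOCF is reproducible only if the last observation is defined without discretion. Here the protocol makes it a matter of judgement for each patient, between two visits at which the patient's state may differ. Several discontinuation reasons concern a change in clinical state, so the two visits can fall on opposite sides of the response or remission threshold. Patients and most staff know the treatment group, and a judgement of this kind is where that knowledge could enter an outcome otherwise protected by the blinded rater.

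The compliance condition is a second, separate weakness. It makes the choice of outcome value depend on whether the patient took the medication after randomisation. A patient who leaves after stopping the drug cannot contribute the exclusion-visit score, so an earlier score is carried forward.

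At stake are the responder and remitter counts, mainly at weeks 9 and 29. The week 2 test is exposed only through patients who leave before then.

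**Working it through.** **1. The plan's own figure.** Section 11 asks for 39 per group to detect 13 − 10 = 3 points with SD 4, type I error 0.05 and power 0.90. The two-sided normal formula gives 2 × (1.960 + 1.282)² × (4/3)² = 37.4, rounded up to 38. The t-test version gives 38.35, rounded up to 39. The figure reproduces and does not bear on this point. Section 12 plans 50 per group, which is used below.

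**2. From the choice to the primary test.** Section 4.6.6 determines which visit's data are collected. LOCF in section 11 uses the last collected value. The responder count in section 4.3 is built from that value. No single sentence says that the chosen score is the one carried forward, but it follows from these three sections.

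**3. Where discretion remains.** Without medication compliance, the exclusion visit is barred. With compliance, it is allowed but not required. The condition is necessary and not sufficient, so it narrows the choice without settling it.

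**4. When the choice changes the outcome.** At the planning baseline of 24 (section 11), response needs a score below 12.
- Score 10: 1 − 10/24 = 58.3% reduction, a responder.
- Score 14: 1 − 14/24 = 41.7% reduction, not a responder.
- Response status differs between the visits if one score is 11 or less and the other 12 or more. Remission status differs if one is 7 or less and the other 8 or more.

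**5. Weight of one patient.** 1/50 = 2 percentage points in that arm. As an illustration with invented counts (chi-square without continuity correction):
- 30/50 against 20/50: chi-square 4.00, p = 0.046.
- 30/50 against 21/50: chi-square 3.24, p = 0.072.

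**6. Range under assumptions.** The protocol gives neither a discontinuation rate nor the share of discontinued patients whose status differs between the two visits. Assume 10–30% for each, and a true response rate of 50% in both arms.
- Patients whose status turns on the choice: 50 × 0.1 × 0.1 = 0.5 to 50 × 0.3 × 0.3 = 4.5 per arm.
- Take an even split of choices as neutral. If every choice in one arm is favourable, that arm's rate rises by half the discordant share: 0.01/2 = 0.5 points to 0.09/2 = 4.5 points. If the choices also run the opposite way in the other arm, the difference shifts by 1 to 9 points.
- Type I error of the nominal two-sided 0.05 test (normal approximation, 50 per arm):

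| Discontinued / discordant | One arm only | Opposite in both arms |
|---|---|---|
| 10% / 10% | 0.050 | 0.051 |
| 20% / 20% | 0.055 | 0.068 |
| 30% / 30% | 0.073 | 0.146 |

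If the choice is made alike in both arms, there is no shift from this source. The table shows what the rule would permit; it is not an estimate of what would happen.

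**The case against.** **Unblinded staff choosing between two known scores.** A reader might infer this, but the protocol does not say it. It does not name the decision-maker, and its wording is about whether to collect data from the exclusion visit. The decision could therefore precede any exclusion-visit rating. This objection stands against the stronger reading. What remains is that nothing requires the decision to be blinded, and the rater who is blinded has no access to the records and CRFs in which drop-out reasons and compliance are kept. Even someone without both scores would know the patient's clinical state.

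**Contradiction with intention-to-treat.** A reader might infer this from the compliance condition. It is too strong. The condition removes nobody; it selects which observation represents a patient who stays in the randomised group. Both arms take duloxetine, and the condition is worded identically for both. It is in tension with the intention-to-treat intent, no more.

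**The worsening example is narrow.** Worsening must continue over two weekly assessments, so the previous regular visit may itself already be a worsened one. This stands: a switch in status needs the threshold to be crossed between those two visits. A patient readmitted after relapse is a clearer case, because the previous regular visit may predate the relapse.

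**The p-values prove little.** The counts are invented, and any single patient's status could tip such a result. This also stands; they show sensitivity, not bias.

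**The mixed model avoids LOCF.** True, but it does not test the primary responder counts, and it too uses whichever scores were collected.

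**This belongs in an analysis plan.** Missing detail would, but here the protocol itself states a discretionary rule.

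**Conclusion.** The point holds as a weakness in how the primary outcome is fixed. The protocol sets a discretionary rule and an adherence condition for the value that LOCF can carry forward, and nothing elsewhere in it removes the discretion. The documents do not show that any bias would occur. Its direction and size cannot be derived, and it may be nil. Under the assumed 10–30% discontinuation and 10–30% discordance, type I error would lie between 0.050 and 0.073 if choices favoured one arm only. It reaches 0.146 only at the top of both ranges with choices running in opposite directions in the two arms. At the low end the effect is negligible. The point should be corrected because the discretion touches the primary outcome in a trial where only one rater is blinded, and because removing it costs almost nothing.

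**What to change.** 1. In section 4.6.6, replace the individual assessment with one rule for both arms: use the blinded rater's HAM-D17 at the exclusion visit when it was obtained, otherwise the last available blinded HAM-D17.
2. Delete the medication-compliance condition for using exclusion-visit data, and record adherence separately.
3. State in advance how patients removed for a MAS score of 15 or more are handled. Such a patient may have a low HAM-D17 at the exclusion visit, and the fixed rule would then carry the patient forward as a remitter. Either count these patients as non-responders or report them separately.

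The cost is a short protocol amendment, with no extra patients and no added scheduled visits. The main downside of the fixed rule is the mania case, which item 3 addresses. Continued rating of patients after they discontinue is a separate suggestion and not needed for this correction.

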**4.7. Biochemical and physical tests**

Blood samples are taken at inclusion to be analysed for TSH (thyreoidea stimulating hormone), haemoglobin, creatinine, alanine transferase, alkaline phosphatase, ionised calcium, folic acid, cobalamin and urine hCG (in women). An ECG is made. Group B patients are asked to collect diurnal urine to be examined for cortisol on the first day of hospitalisation and again after 9 weeks, at the end of the study. On the second day of hospitalisation, group B patients give saliva samples, also for cortisol analysis. This provides an opportunity for comparing cortisol in diurnal urine and saliva. The saliva samples are taken in the morning, 15, 30 and 60 minutes after awakening.

Blood pressure is measured at inclusion and after 9 weeks by automatic blood pressure monitor while the study subject is seated. The measurement is repeated several times, until the blood pressure is reproducible. The value from the arm giving the highest result will be used. ECG is made at inclusion and is assessed by a doctor with medical expertise.

**5. COMPLIANCE**

Is ensured by close monitoring of the completion of sleep diary, light diary, exercise diary, and by drug accountability.

Drug accountability:

- Medication prescribed for a non-psychiatric condition (physical illness) is to be administered by the study subjects. Any help in administering the medication is to continue unchanged.
- Drugs prescribed for a psychiatric condition (including hypnotics, anxiolytics and mood stabilisers) have to be brought along at each visit, where the amount taken is checked and recorded in the CRF. The medication given to the patient covers the time until the next visit. For patients who have problems taking their medication, the drug will be distributed into dosing boxes. This medication is thus fully administered by the investigators.

Diaries:

- Compliance to the recommendations regarding sleep, diurnal rhythm, exercise and light are monitored by means of the relevant diaries, which are brought along at each visit. The diaries are kept throughout the whole study.

**6. SOURCE DATA**

The various types of source data are kept as follows:

| Inclusion and exclusion criteria | CRF |
| --- | --- |
| Demographic (anamnestic) data | CRF |
| Blood pressure, height and weight | CRF |
| Concomitant medication | CRF |
| Laboratory tests | Patient record |
| Study medication accounts | CRF |
| Side effects | CRF |
| Primary effect parameters (severity of depression) | CRF |
| Secondary effect parameters (severity of depression) | CRF |
| Tertiary effect parameters (exercise) | CRF |
| Tertiary effect parameters (cortisol) | Patient record |
| Tertiary effect parameters (idiographic method) | CRF |
| Tertiary effect parameters (Preskorn) | CRF |
| Medication (prescribed) | Patient record |

All source data will be kept at Frederiksborg General Hospital, Dept. of Psychiatry, for 15 years.

**7. PATIENT RECORDS**

Patient records are kept with a summary of the patient's case history. For each visit the patient's condition is described, side effects are recorded, and a measurement of severity of depression is made. Skipped visits and the reason for not showing up are also recorded. The patient record is kept separately from a possibly existing patient record at the hospital in a locked room and filed under the patient number.

**8. PATIENT INFORMATION AND INFORMED CONSENT**

Potential study subjects who are interested in information about the study will receive written information about the study and its single elements, e.g. that patients will be hospitalised at the psychiatric hospital for 6 days. An appointment is made with the patient for oral information on the study. Both written and oral information will be given according to the rules on information to and consent by patients, published by the Danish Ministry of Science in 2003, Committee Act on information and consent when involving study subjects in biomedical research projects. (" Act on a Biomedical Research Ethics Committee System and the Processing of Biomedical Research Projects"). See also under selection of patients.

**9. CONTACTS WITH TREATING MEDICAL PROFESSIONALS**

If the patient agrees, short statements will be sent to the referring doctor and the patient's GP, with relevant information about the trial and the outcome for the patient at inclusion and at end of the study. All correspondence with public authorities, among them sick reports and medical certificates, are made by the patient's GP unless the patient explicitly wishes the investigator to do it.

**10. SAFETY ASSESSMENT**

Side effects during treatment are recorded by means of the UKU at each visit. The reporting of side effect is made according to GCP rules requiring that side effects are reported and that a final debriefing report is sent to the Danish Medicines Agency. Thus, all unexpected and severe presumed side effects which are lethal or life-threatening, have to be registered and reported as soon as possible, 7 days after the event has been made known to the investigator at the very latest. Not later than 8 days after the report the investigators will inform the Danish Medicines Agency about follow-up to the report. All other unexpected and serious presumed side effects must be reported 15 days after being made known to the investigator, at the very latest. Each report will be accompanied by comments concerning the possible consequences for the study.

The following definitions will be used according to the guidelines for clinical trials by the Danish Medicines Agency:

"Adverse event: any adverse event experienced by a patient or a study subject in a trial after treatment with a drug, though there may not be any connection between the treatment and the adverse event experienced.

Side effect: any harmful and adverse reaction to a trial drug regardless of dose.

Unexpected side effect: a side effect the severity or character of which are not in agreement with the product information (e.g. the investigator's brochure for a non-licensed trial drug or, if the drug is licensed, the product summary).

Serious adverse event or severe side effect: an event or a severe side effect that irrespective of dosage leads to death, is life-threatening, leads to hospitalisation or extension of current hospitalisation, permanent or serious disability, incapacity for work, or results in congenital anomaly or deformity.

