4.1.4. Hospitalisation phase: week 1 (7 days)

All study participants are hospitalised and meetings with the study investigators are envisaged for each working day. All patients (both groups, A and B) are hospitalised in an open in-patient ward. See Figures 1 and 2. Previously hospitalised patients can be discharged if their condition permits it. Patients admitted due to study participation will be discharged 6 days after admission unless their condition does not allow it. If the patient stays in hospital the trial will follow the usual guidelines, but the visits will take place in the in-patient ward whenever necessary.

Group A

- During hospitalisation, Group A patients go through 3 sleep deprivations, the first one on the day of admission (see Figure 2). Sleep deprivation is mainly carried out as total sleep deprivation, i.e. the patients stay awake all night. However, in some cases partial sleep deprivation may be used, in which the patient is woken up at 02.00 a.m. and has to stay awake for the remains of the night. This can be done either due to an individual patient evaluation made by the investigator or due to a wish on the part of the patient. There may be good reason for using partial sleep deprivation in case of medical diseases such as diabetes, where the blood sugar level can get out of balance, or in other diseases that may be influenced by a longer wake period. Also elderly patients expect not to be able to stay awake all night may also profit from partial sleep deprivation. Patients who experience that their first and total sleep deprivation is too demanding may also switch over to partial sleep deprivation. A combination of total and partial sleep deprivation is thus permitted.
- In the evening after each sleep deprivation the patients must go to bed at 9 p.m. at the very latest and get up at 7 a.m. the following morning (sleep-phase advance).
- The treatment with duloxetine continues unchanged, with a dose of 60 mg daily.
- The patients are informed about light treatment on the day of admission which is given for the first time the following morning and subsequently each day of the study period. The duration of light treatment is 30 minutes. The time of day of the light treatment is decided after completion of the MEQ questionnaire (see psychometrics paragraph). In addition to this, to fight tiredness, the patients take light treatment at 4 a.m. each night during the period of sleep deprivation.

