To decide at which hour light treatment should be administered, the Morningness-Eveningness Questionnaire (MEQ) will be used (Horne et al. 1976, Horne et al. 1977, Terman et al 2005).

Side effects will be rated by means of the UKU (Udvalget for Kliniske Undersøgelser, evaluation form for side effects) (Lingjærde et al. 1987), with relevant questions concerning serotonergic and noradrenergic side effects.

The Mania Scale (MAS) is to be used at all visits to assess the possible development of a hypomanic or manic condition. A MAS score of 15 or more thus means exclusion from the study.

The SPAQ (Seasonal Pattern Assessment Questionnaire) (Kasper et al 1989) questionnaire will be used to assess seasonal variability of the depression.

The idiographic method is to be used at all visits, but only in group B patients. The method implies free constructs by the patients who describe the symptoms they have experienced in connection with their current depressive episode. At each visit, the free construct is given as a percentage value in relation to the baseline construct (set 100% for each construct at baseline, e.g. how much of 100% tiredness is your tiredness today?), thus measuring change from inclusion an onwards. In contrast to the other scales used in the study, this method is not an absolute measure of severity. With this method we hope to obtain a more balanced picture of the symptoms we obtain by standardised methods such as questionnaires and rating scales, and we also hope to accomplish a greater degree of sensitivity towards change in the condition. The strength of this method is that symptoms which patients have experienced during their depression are not forced into the standardised boundaries of a rating scale or a questionnaire. The method is based on Kelly's ideas on free constructs (Kelly, 1955). It has been used in GRID-QOL (Thunedborg et al 1995), a computer-assisted quality of life rating system.

At inclusion, sleep and exercise are evaluated for both groups. Sleep diaries, exercise diaries and medication diaries are completed in both groups at each visit. Light diaries are only completed in group A.

The scales are employed as indicated in flowcharts 1 and 2. Flowchart 1 covers the first 9 weeks while flowchart 2 covers weeks 10 to 29.

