4.6.4. Exclusion criteria

- - Clinically dominant psychic or somatic anxiety corresponding to a score of 3 or more on items 10 and 11 (score range from 0 to 4) of the Hamilton Depression Scale (HAM-D17).
  - Clinically domonating suicidal ideation corresponding to a score of 3 or more (score range from 0 to 4) on item 3 of the Hamilton Depression Scale (HAM-D17), or if patient or investigator are not certain about the degree of suicidality.
  - Alcohol or drug abuse as defined in the M.I.N.I.
  - Epilepsy, as seizures can be triggered by sleep deprivation.
  - Unsafe contraception in women in the reproductive age. ½Safe contraceptive methods are: contraceptive pills, sterilisation, gestagen depot injections, subdermal hormone implantations, hormonal vaginal rings and transdermal depot patches. It is required that fertile women as a minimum use one of these methods over the total study period and two months after the end of the study.
  - Pregnant and lactating women. All women are pregnancy-tested by a urine sample test.
  - Psychotic disorder as defined in the M.I.N.I
  - Antisocial personality disorder as defined in SCID.
  - Borderline personality disorder as defined in SCID.
  - Schizotypal personality disorder as defined in SCID.
  - Clinically significant organic brain disorder or mental retardation causing incapacity.
  - Treatment with antipsychotics
  - Treatment with drugs with a well-known and significant interaction with duloxetine, e.g. isocarboxazide, thioridazine and fluoxetine. Patients in fluoxetine treatment may be included after one week's discontinuation of treatment.
  - Clinically significantly reduced kidney or liver function.
  - ECG abnormalities which may be of clinical significance in connection with the study or study medication.
  - High blood pressure not treated by medication
  - Glaucoma
  - Patients equally fulfilling the M.I.N.I. criteria for major depression and mania or hypomania and thus suffering from a mixed condition.
  - Patients who have a record that makes it doubtful that they can comply with the guidelines of the study (expected low compliance).
  - Patients who due to their medical history or physical tests during the screening procedure were found to have signs of a somatic condition requiring treatment.
  - Patients with bipolar disorder who have not been treated with a mood stabiliser for at least one month.
  - Allergy to filler components of duloxetine tablets.

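### Expedited safety reporting in section 10 covers only presumed reactions to a trial drug, so unexpected serious harms of the randomised non-drug components have no expedited route

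*Protocol*

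**What the plan says.** Protocol section 10 sets out both recording and reporting.

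- Recording: "Side effects during treatment are recorded by means of the UKU at each visit". Section 4.2 describes the UKU as used here "with relevant questions concerning serotonergic and noradrenergic side effects".
- The basic definition is tied to the drug: "Side effect: any harmful and adverse reaction to a trial drug regardless of dose".
- The test for whether such a reaction was foreseen is tied to the drug's documentation: "a side effect the severity or character of which are not in agreement with the product information".
- 7-day rule: "all unexpected and severe presumed side effects which are lethal or life-threatening, have to be registered and reported as soon as possible".
- 15-day rule: "All other unexpected and serious presumed side effects must be reported 15 days after being made known to the investigator".

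Section 10 also defines an adverse event with no causal link required, and its seriousness category covers events as well as side effects. Section 23 asks for a yearly list of presumed serious adverse events and a safety report to the agency. The source-data table in section 6 has a row for side effects and none for adverse events. Section 7 has side effects recorded at each visit, together with a description of the patient's condition and a depression rating.

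Duloxetine is given to everyone (section 2.1). The randomised contrast is sleep deprivation, light and diurnal-rhythm maintenance against an exercise programme (section 3).

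**The concern.** The trial tests non-drug interventions, but its expedited reporting is written for the drug that both groups share. The protocol does not treat those interventions as harmless. It excludes "Epilepsy, as seizures can be triggered by sleep deprivation". It allows partial deprivation in diabetes, "where the blood sugar level can get out of balance, or in other diseases that may be influenced by a longer wake period". Section 2.2 puts the risk of manic switch after sleep deprivation on a par with that of antidepressants. Section 20.2 provides for a longer hospital stay if a patient unexpectedly gets worse after sleep deprivation, and says patients must be told about its side effects, a use of the term that section 10's definition does not allow.

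At stake is how promptly the agency hears of an unexpected serious harm from the intervention under test. The sponsor is also the investigator (section 1.3) and no interim analysis is planned (section 11), so expedited reporting is a main route for that information.

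**Working it through.** The protocol gives no safety figure to reproduce. The check is to follow a serious event through section 10 as written.

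**Step 1: is it a side effect?** The definition requires a reaction to a trial drug, and duloxetine is the only one. An event attributed to sleep deprivation, light, sleep-phase advance or exercise, and not to duloxetine, does not qualify.

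**Step 2: is it unexpected?** The comparison is with the drug's product information. Section 10 names no reference for any non-drug component.

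**Step 3: does a clock start?** The 7-day and 15-day rules both require an unexpected presumed side effect. An event that fails step 1 starts neither, however serious it is. Unexpected worsening after sleep deprivation that lengthens an admission shows the mismatch: it meets section 10's own seriousness test, which includes prolonged hospitalisation, but it is not a side effect as defined.

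**Step 4: is it captured by another route?** In part.

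- The adverse-event definition would include it, since every participant is on duloxetine and no causal link is needed.
- Flowcharts 1 and 2 schedule the UKU and the Mania Scale at every visit in both groups, so manic symptoms are rated whatever their cause.
- Section 7 requires a description of the patient's condition at each visit.
- Section 23's yearly list could include it, but a yearly list is not expedited, and the protocol describes no collection step that feeds it.

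Sections 6, 7 and 10 name only side effects as the item to be recorded. Capture of other events therefore depends on what the UKU happens to ask and what the clinician chooses to note.

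**Step 5: exposure.** Section 12 plans 50 patients per group.

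- Planned deprivation nights in the hospitalisation week: 50 × 3 = 150.
- Upper limit, if every Group A patient qualifies for and accepts two more (section 4.1.5): 50 × (3 + 2) = 250.
- If every patient omits the one deprivation that section 4.6.6 tolerates and none has the extra two: 50 × 2 = 100.

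These counts show how much exposure the rule leaves out. They say nothing about how often harm occurs, and the point does not depend on them.

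**The case against.** The strongest reply is that the protocol observes patients more closely than section 10 alone suggests. Besides the UKU, the Mania Scale and visit notes, meetings are envisaged on each working day in hospital, with daily HAM-D6 ratings. Patients are assessed in the ward before discharge after the additional deprivations. Mania Scale scores of 15 or more, continued worsening and re-admission are discontinuation criteria in the first nine weeks, and reasons for drop-out go into the CRF. The UKU form and the CRFs are enclosures that are not shown, so their content cannot be judged from one phrase. All of this stands. A reader might infer that harms of the randomised components are never recorded, and the protocol does not support that.

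A reader might also infer that harms will not be compared between groups. That would rest only on the silence of section 11. Safety tabulation is commonly left to a statistical analysis plan, which is not at hand, and the same UKU and Mania Scale data exist in both arms.

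Two further replies have some force. Every patient deprived of sleep is already on duloxetine, and a reaction need only be presumed, so a site might report a seizure as a possible drug reaction. That would work only by attributing to the drug an event the investigator may believe has another cause. Secondly, section 10 presents its definitions as those of the medicines agency's trial guidelines. This explains the drug-centred wording and argues against any intent to conceal, but it does not make the wording suit a trial whose randomised components are not drugs.

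Finally, harms that the protocol foresees might count as expected, and so not be expedited, even under a wider definition. This is correct, and it means that redefining the side effect is not enough: an expectedness reference is needed too.

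**Conclusion.** The point holds for expedited reporting. The definition of a side effect, the test for unexpectedness and both reporting clocks are tied to the drug, so unexpected serious harms attributed to sleep deprivation, light, sleep-phase advance or exercise have no 7-day or 15-day route. On recording, a more limited statement holds: adverse events are defined regardless of cause, but no section sets out their systematic collection, and capture of non-drug harms is partial.

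The gap covers every planned participant's randomised intervention, including the 100 to 250 deprivation nights counted above. No event rate, and no bound on one, can be derived from it. The conclusion assumes that section 10 is applied as written and that the unseen enclosures contain no separate adverse-event form. If they do contain one, the recording part falls and the reporting part remains. This is a flaw of wording and scope that should be corrected. It does not invalidate the efficacy comparison.

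**What to change.** In section 10:

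1. Define a side effect as a harmful reaction to any study intervention: duloxetine, sleep deprivation, light, sleep-phase advance or exercise.
2. Apply the 7-day and 15-day reports, and the yearly list in section 23, to side effects so defined.
3. Name the reference against which expectedness is judged for the non-drug components. The publications on the chronobiological methods that section 18 already places in the investigator's brochure could serve for those they cover; exercise may need its own source.
4. Record adverse events by the protocol's existing definition, with the presumed attribution, on the CRF at each visit in both groups and during the sleep-deprivation admissions. Add a matching row to the source-data table in section 6.

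The cost is one CRF page, revised wording in sections 6, 10 and 23, and somewhat more reporting. No treatment, visit or efficacy measure changes.
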